### *Postnatal Depression*

Our primary measure is the Edinburgh Postnatal Depression Scale (EPDS; Cox, Holden & Sagovsky, 1987)(Appendix C) . The EPDS is a 10 item self-report scale designed to screen for postnatal depression in nonclinical populations. Participants give one of four possible responses to each of the ten statements. These possible responses indicate frequency, e.g. ranging from “Not at all” to “Yes, most of the time”, but the exact wording varies according to the statement. The scale typically takes around 5 minutes to complete (Cox et al., 1987).

The EPDS has been used widely in the National Health Service (NHS) as a screening tool for post-natal depression; and in previous studies in the field of maternal mental health and wellbeing (Leahy-Warren, McCarthy & Corcoran, 2012). A number of past studies found this scale to be a valid and reliable (Cox & Holden, 1994; Pope & Pope, 2000). In 2017, Cox published a 10 point supplement to their previous manual for this scale, designed to assist researchers in avoiding misuse of the EPDS (Cox, 2017). This study aims to follow both the manual for the scale (Cox, Holden & Henshaw, 2014), and this supplement (see Appendix D), in order to ensure standardised practice.

Because this measure is the primary screening tool for PND used in the NHS, if a participant scores above the clinical threshold implemented in the NHS, they will be sent a letter informing them of this, and encouraging them to access assessment and treatment for

postnatal depression via their GP or health visitor. This letter can be found in Appendix E.

At all three data collection time-points, information will be collected around whether participants are currently accessing pharmacotherapy or psychological care, using specific mental health-related items (please see Appendix B). This is in order to control for this variable during data analysis.

Recent studies have found that the sensitivity and specificity of the EPDS can vary between 59% to 100% and 44% to 97% (respectively) according to the geographic location of the study, the cutoff scores chosen by researchers, and the reference standards used for diagnosis (Novotney & Maurer, 2017).

Due to this variability in terms of sensitivity and specificity, some studies have recommended supplementing the EPDS with a second validated measure of depression that has shown less variation in sensitivity and specificity (Miller, Pallant, & Negri, 2006).

While a number of studies have used the Beck Depression Inventory (BDI; Beck et al., 1961) or Patient Health Questionnaire (PHQ-9; Kroenke, Spitzer, & Williams, 2001) measures in this way (Moraes, Lorenzo, Pontes, Montenegro, & Cantilino, 2017), Miller et al., suggest that these measures are not valid for use with a postnatal population, as often the items included in these measures are experiences that commonly occur following birth (e.g. increased tiredness, change in eating patterns, change in sleeping).

For this reason Miller et al., elected to supplement the EPDS with the Depression Anxiety and Stress Scales (DASS; Lovibond & Lovibond, 1995). The DASS does not include these items that have been identified as potentially confounding within measures such as the BDI (Miller et al., 2006). It was originally designed as a measure that distinguished between symptoms of Anxiety and those of Depression, and subsequently was found to also identify a third symptom group, that the authors labelled as “stress” (Lovibond & Lovibond, 1995). The

DASS has established reliability and validity with both non-clinical and clinical populations (Ng et al., 2007). Miller et al., argue that the DASS offers “a more complete picture” of maternal mood following childbirth, because it is a general measure of “postnatal distress”, including anxiety and stress rather than focusing on depression alone. Furthermore this measure has been found to be sensitive to mild presentations of these conditions, thus not only capturing those with severe symptomatology and instead identifying a range of levels of distress.

The original DASS consists of 42 statements. Participants indicate the degree to which they feel each statement has applied to themselves over the last week, using a four-point Likert scale ranging from “Did not apply to me at all” to “Applied to me very much, or most of the time”. For the sake of brevity, this study will be using the DASS-21 (Appendix F), a version of the DASS that includes only 21 statements. The DASS-21 has been widely used with both clinical and non-clinical populations and has been found to have strong concurrent validity with other measures, such as the BDI, and the Beck Anxiety Inventory (Beck, Epstein, Brown & Steer, 1988) (Le et al., 2017).

### *Attachment*

We will use the Experiences in Close Relationships Scale (12 item version; ECR-12) (Lafontaine et al., 2015) (see Appendix G) as a measure of attachment. This is a 12-item version of the original 36-item Experiences in Close Relationships Scale (ECR) (Brennan, Clark & Shaver, 1998). The ECR and ECR-S are used to evaluate adult attachment style. They contain 12 and 36 statements respectively, which participants rate from 1 (strongly disagree) to 7 (strongly agree) using a 7-point likert scale. Both produce two scores labelled *Anxiety* and *Avoidance*. The ECR is a well-validated and reliable measure, and the ECR-S has been found to have validity equivalent to that of the ECR (Wei et al., 2007).

### Secondary Measures

#### *Wellbeing*

This study aims to examine the impact of sling use upon both maternal mental health and maternal wellbeing. Currently, mental wellbeing is seen as more than the absence of mental health difficulties (“Promotion of mental well-being”, n.d.), with these constructs viewed as separate rather than two ends of the same scale (Tennant et al., 2007). Thus it seemed appropriate to also include a separate measure of wellbeing to administer alongside the DASS and EPDS.

The Warwick Edinburgh Mental Wellbeing Scale (WEMWBS; Tennant et al., 2007) is a 14-item scale designed to measure and monitor mental wellbeing in the general population (“Warwick Edinburgh Mental Wellbeing Scale (WEMWBS)”, n.d.). The items are worded positively, with participants rating each statement on a five-point Likert scale from “None of the time” to “All the time”.

The WEMWBS has been validated for use with people aged 13 to 74 in both clinical and non-clinical populations. (Tennant, et al., 2007; Clarke, et al., 2011; Stewart-Brown et al., 2009; Maheswaran, Weich, Powell, & Stewart-Brown, 2012; Stewart-Brown, 2013). Crawford et al., (2011) found that service users find the WEMWBS easy to complete and prefer this scale over other mental health scales. The WEMWBS has been used previously with mothers who have recently given birth (McKellar, Steen & Lorensuhewa, 2017; Mustaffa, Marappan, Abu, Khan, & Ahmad, 2014). Therefore this measure will be used as a primary measure of maternal wellbeing within this study (Appendix H).

There is a short 7-item version of the WEMWBS (the SWEMWBS, Appendix I),

which may be used in this study if the battery of measures becomes too onerous. This version has been found to have adequate internal consistency and reliability (Haver, Akerjordet, Caputi, Furunes, & Magee, 2015).

### *Parenting*

The Parenting Sense of Competency Scale (PSCS; Gibaud-Wallston & Wandersman, 1978)(Appendix J) will be used to measure parental self-efficacy. This scale measures two dimensions of parental competence: Satisfaction and Efficacy. It is a 16-item likert-scale questionnaire in which participants give responses ranging from “strongly agree” (1) to “strongly disagree” (6). There are nine questions for the dimension of Satisfaction (examining the parents’ perceived anxiety, motivation and frustration), and seven assessing Efficacy (parents’ perceived competence, capability and problem-solving abilities). This scale has been validated (Ohan, Leung, & Johnston, 2000).

Following the example of Cutrona & Troutman (1986), and again, following feedback from service users, this study may, for the sake of brevity, use only the seven Efficacy items.

The Caregiving Experiences Questionnaire (CEQ; Brennan, George & Solomon, 2013) will also be used as a parenting measure within this study, assessing the nature of each participating mother’s relationship with their child. The CEQ is a measure designed to assess 5 dimensions of the parent-child relationship. These dimensions have emerged from attachment theory and include “enjoyment, discourages closeness, heightened, helplessness, and role reversal” (Brennan et al., 2013). Each item of this scale is a statement designed to examine a mother’s evaluations of themselves, their child, and their relationship with their child. Altogether the CEQ contains 40 of these statements (Appendix K), with mothers asked

to endorse items using a five-point Likert scale ranging from “Not at all characteristic” (1) to “Very characteristic” (5). The CEQ was developed and validated in a US population.

Research investigating the validity of this measure in non-US populations is ongoing (Røhder et al., 2018).

Lastly, a measure of infant stroking by mothers has been included in the battery of questionnaires. This is because recent literature has highlighted possible associations between maternal mental health and maternal stroking (Sharp, Pickles, Meaney, Marshall, Tibu, & Hill, 2012). A measure developed by Sharp et al. (2012), which was designed for use in the community, will be used in this study also (please see Appendix N).

### *Infant Temperament*

This study will use the Infant Behaviour Questionnaire-Revised Very Short Form (IBQ-R VSF; Putnam, Helbig, Gartstein, Rothbart, & Leerkes, 2014) to measure infant temperament. The original Infant Behaviour Questionnaire (IBQ; Rothbart, 1981) consisted of six scales assessing “Activity Level, Fear, Distress to Limitations, Smiling and Laughter, Soothability, and Duration of Orienting”. The revised version (IBQ-R; Gartstein & Rothbart, 2003) added several new scales (“Approach, Vocal

Reactivity, High and Low Intensity Pleasure, Perceptual Sensitivity, Sadness, Falling Reactivity, and Cuddliness”) resulting in a measure that consisted of 191 items in total. Putnam et al., recognised that, while it may be important to capture the wide range of characteristics that may be regarded as aspects of temperament, there is a limit to the demands that researchers may place upon participants in terms of both time and effort. In order to “resolve this conflict”, Putnam et al., developed the IBQ-R Short Form (91 items total) and the IBQ-R VSF (37 items total).

Due to the number of measures already included in the batteries that will be administered to our participants at each time-point, this study has opted to use the IBQ-R VSF (Appendix L). This version of the IBQ assesses three broader factors involved in infant temperament: Negative Emotionality (NEG), Positive Affectivity/Surgency (PAS), and Orienting/Regulatory Capacity (ORC). The 14 “fine-grained” scales examined in the IBQ-R make up these wider factors. For example, Putnam et al., propose that NEG is made up of the Sadness, Distress to Limitations, Fear, and Falling Reactivity scales, while PAS consists of the Approach, Vocal Reactivity, High Intensity Pleasure, Smiling and Laughter, Activity Level, and Perceptual Sensitivity scales. Finally ORC is made up of the Duration of Orienting, Low Intensity Pleasure, Cuddliness, and Soothability scales.

In all versions of the IBQ, participants are asked to use a seven-point Likert scale, ranging from “Never”(1) to “Always”(7), to indicate the frequency with which their child has displayed specific behaviours within certain situations (e.g. “When tired, how often did your baby show distress?”) over the past week. The scale also includes a “Not Applicable” option in case one (or more) of the situations described, had not arisen over the past week.

With regards to validity, the IBQ and IBQ-R are two of the most frequently used measures of infant temperament (Putnam et al., 2014). A number of studies have found these measures to have validity equal to observational measures of infant temperament (Gartstein et al., 2010; Gartstein & Marmion, 2008; Kochanska, Coy, Tjebkes, & Husarek, 1998; Parade & Leerkes, 2008). Peterson et al., (2017) found that the IBQ-R VSF has “promising reliability and predictive validity in a large, diverse sample.”

### *Perceived Social Support*

A shortened, 5-item, version of the Social Provisions Scale (SPS; Russell & Cutrona, 1984), which has been used in previous studies and shown to correlate with the full, validated, SPS (Cutrona & Troutman, 1986) will be used to measure perceived social support. The SPS measures the six aspects of social support identified by Weiss (1974). Each item is a statement (specified in Cutrona & Troutman, 1986; please see Appendix M), which participants rate on a 7-point likert scale, from “Not at all true” to “Completely true”.

### *Demographic Measures*

Data will be collected around the following:

Age, postcode, ethnicity, mental health, physical health, first born vs. latter born, how they have heard about the study, socioeconomic status, whether the person has a partner, and years in education.

Please see Appendix O.

### *Breastfeeding*

Information will be collected around mothers’ feeding methods (i.e. whether they are breastfeeding or tend to formula feed) over the course of the study. This breastfeeding item has been integrated into the demographics questionnaires, but, unlike the demographic questions, will be re-administered at the final data collection time-point (Please see Appendix O).

### *Qualitative Questions*

Qualitative data is commonly collected in feasibility studies, as it can help to improve the design of future trials, including intervention content, and the selection of relevant outcome measures in order to support greater measurement completion (O’Cathain et al.,

2015).

Therefore, at T3, all participants will be given qualitative questions about their experience of participating in the study, and their experience of using a sling and accessing the Sling Surgery services, to answer online. These questions will be phrased as open questions and will be formatted as free-text boxes on Qualtrics, rather than having any set response options. They may be found in Appendix P.

The exact wording of these questions may change following service user feedback.

## Procedure

Participants will be recruited while they are pregnant. When recruited, participants will be provided with further information, complete consent forms and provide contact details via the software programme Qualtrics (please see Appendices P-R), then be randomised to one of two conditions: an intervention condition or a waitlist control condition. This randomisation will not be blind.

Participants will be allocated to each condition using a computer generated randomisation list. This will follow a 1:1 randomisation ratio (1 intervention participant per each control participant) so that there are equal numbers of participants allocated to each condition.

Once they have consented to participating, participants will be sent an email containing a link to the online baseline measures. This email will ask them to complete these measures when their child is between 0 and 6 weeks of age.

Participants will be sent a text reminder around the time of their due date (unless they have requested an email or no reminder instead), reminding them to complete these measures.

This text or email will again contain the link to the baseline measures in case they no longer have access to their first email.

Example templates of the emails and/or texts that may be sent to participants, as well as the information that may be shown to participants via Qualtrics when they are completing each battery of measures at each time-point, may be found in Appendix S.

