### Inclusion Criteria

This study aims to recruit expectant mothers whose due dates fall within the expected baseline data collection period (late February 2019 to July 2019).

This study aims to recruit women who have not already been a regular sling user (e.g. with a previous infant).

Participants will need to be able to travel to Sheffield Sling Surgery (Sheffield city centre) where the intervention will take place. This includes all participants, as those randomised to the control group will receive the intervention following trial completion.

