### Exclusion Criteria

Participants will be excluded from this study if they have used a sling previously or attended an antenatal workshop at a sling library. They will also be excluded if their infant has a chronic or serious illness, or a disability. This is because the sling library have advised that that parent-infant dyads for whom this is the case often require a greater level of support and training when using a sling than this study would be able to provide (Knowles, 2016). Any participants who are interested in the study, but get excluded on this basis, by definition meet the inclusion criteria for the charitable “Building Bonds” scheme, currently running at the sling library, offering free sling hire, training and support specifically for families with chronic conditions and disabilities. These individuals would be referred to this scheme, and so will not be disadvantaged by the exclusion criteria.

As it is a feasibility study, this study has few inclusion and exclusion criteria. However data will be collected regarding any mental health diagnoses, number of children prior to their current infant, participant age, socioeconomic status, ethnicity, education level, postcode, and whether they are in a relationship or not. During data analysis, the impact of these factors upon the results of the study will be examined in order to potentially inform inclusion and exclusion criteria of future RCTs.

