**Have you attended any antenatal sling workshops during this pregnancy or any previous pregnancies?**

- ☐ Yes  
☐ No

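### Randomising at consent in pregnancy puts the infant-health exclusion and the T1 baseline after allocation, and contradicts the Abstract on who is randomised

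*Protocol*

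**What the plan says.** **Order of steps.** Procedure: "Participants will be recruited while they are pregnant". They read the study information, consent, give contact details and "then be randomised to one of two conditions: an intervention condition or a waitlist control condition. This randomisation will not be blind". Of the message carrying the baseline link it says: "This email will ask them to complete these measures when their child is between 0 and 6 weeks of age". The Intervention and Data Collection sections place T1 before the sling session, and the invitation to that session follows completion of T1.

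**Abstract.** It describes the randomised population as mothers whose infants are already born and up to six weeks old.

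**Eligibility.** Exclusion Criteria, on mothers: "They will also be excluded if their infant has a chronic or serious illness, or a disability". Prior sling use is worded two ways. The Inclusion Criteria seek "women who have not already been a regular sling user", while under the Exclusion Criteria women are "excluded from this study if they have used a sling previously". Attendance at an antenatal sling-library workshop also excludes. In the forms shown, that item ("Have you attended any antenatal sling workshops during this pregnancy or any previous pregnancies") is in Appendix O, which is headed as part of the T1 battery. The sign-up page (Appendix S.2) asks for name, referral source, due date and contact details, with no eligibility item.

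**Analysis and size.** Proposed Analysis names intention-to-treat as the way to deal with drop-out and a mixed ANCOVA comparing pre- and post-intervention scores within and between groups. Sample Size sets 50-60 women, 25-30 per condition.

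**The concern.** A baseline score and an eligibility check normally come before allocation, so that everyone randomised is known to be eligible and has a starting value. Here both come later, possibly by months. Three things are at stake.

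- **Analysis set.** A woman excluded after birth, or who never opens the T1 link, has been randomised but has no pre-score. She falls outside the pre/post comparison on which the stated intention-to-treat analysis relies.
- **The feasibility estimates.** The study exists to inform recruitment, drop-out and sample size for a later trial. Women lost around the time of birth, before anything was offered, become post-randomisation losses. A later trial that randomised at T1 would plan on too high a drop-out rate.
- **The baseline itself.** Randomisation is declared not blind, and nothing says that the arm is withheld until T1. If a woman did learn her arm in pregnancy, her T1 answers, her decision to complete T1, or a control's decision to get her own sling could depend on it.

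**Working it through.** **1. Order of events against each criterion (Procedure section)**

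Consent → randomisation → birth → T1 → sling session.

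| Criterion | Can be known at consent? | Where asked in the forms shown |
|---|---|---|
| Due date in window | Yes | Sign-up page, S.2 |
| Prior sling use | Yes | Poster (Appendix A.1) states it; not on S.2 |
| Antenatal sling workshop | Up to that date | Appendix O, within T1 |
| Ability to travel | Yes | Poster mentions the travel; not on S.2 |
| Infant illness or disability | Generally not before birth | No item in the forms shown |

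So one exclusion is generally settled after allocation whatever is asked at sign-up, and a second is asked after allocation in the forms shown. If the Abstract is followed instead, birth precedes randomisation and the conflict over infant health largely disappears. The two sections describe different designs.

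**2. First arm-specific contact**

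The welcome email (S.4), reminder (S.5) and Qualtrics introduction (S.6) are common to both arms. The first text that differs by arm is the T1 end page (S.7 intervention, S.9 control), followed by the S.8 email. No arm-specific step in the templates needs allocation before T1 is submitted.

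**3. Sample size**

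2 × 25 = 50 and 2 × 30 = 60, which agrees with the protocol. The figure is not power-based and has no stated allowance for loss between randomisation and T1.

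**4. Illustration of pre-T1 loss**

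The protocol gives no rate, so d = 5-30% is an assumption. Number with a baseline = N(1 − d). Number to start with so that 50-60 have a baseline = N/(1 − d), rounded up.

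| d | With a baseline, of 50-60 | Needed at the start |
|---|---|---|
| 5% | 47.5-57 | 53-64 |
| 10% | 45-54 | 56-67 |
| 20% | 40-48 | 63-75 |
| 30% | 35-42 | 72-86 |

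**5. Effect on the drop-out estimate**

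Assume that 10% of women with a T1 score are lost by T3. With 10% lost before T1, loss counted from randomisation is 1 − 0.90 × 0.90 = 19%. With 20% lost before T1 it is 1 − 0.80 × 0.90 = 28%. A trial randomising at T1 would need the 10%.

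**6. Bias if pre-T1 loss differed by arm**

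Assume T1 completion of 90% in one arm and 75% in the other, and a correlation r of 0.2-0.3 between the tendency to complete and wellbeing. The mean of the selected top fraction p of a standard normal variable is φ(z)/p:

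- p = 0.90: 0.195
- p = 0.75: 0.424
- difference 0.229; times r = 0.2 gives 0.046 SD, times r = 0.3 gives 0.069 SD.

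The standard error of a two-group mean difference is √(2/n) SD: √(2/25) = 0.28 and √(2/30) = 0.26. The assumed bias is at most 0.069/0.26 = 0.27 of one standard error.

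**The case against.** **A reader might infer that women know their arm before T1 and answer accordingly.** The documents do not support that. Every template up to the end of T1 is common to both arms, and the statement that randomisation is not blind does not say who knows the allocation or when. The information sheet and consent form (Appendices Q and R) are not available for review. Expectation effects, early sling use by controls and unequal loss are therefore possibilities that the protocol does not rule out.

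**A reader might also infer that maternal criteria go unscreened before randomisation.** That is not shown either. The recruitment poster already asks for women who have not used a sling, the Exclusion Criteria speak of interested women being excluded and referred elsewhere, and the missing appendices may contain screening text. The workshop item covers the current pregnancy, so asking it after birth also catches attendance after sign-up. Only infant health is shown to be settled after allocation.

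**Some consequences are partly handled.** The planned CONSORT flow diagram can show losses by stage. Sling use by controls is a named feasibility question, is measured at T1, and has a planned re-analysis. How missing T1 scores are treated may properly sit in a statistical analysis plan. The study is also declared underpowered for effectiveness, and the bias in step 6 is small even if its assumptions are granted.

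These points remove the claim of demonstrated bias. They leave the order of events, the contradiction with the Abstract, and the fact that randomised women can lack a baseline before any intervention is offered.

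**Conclusion.** The point holds as a matter of sequence. As the Procedure is written, T1 is pre-intervention but post-allocation, at least one exclusion generally falls after randomisation, and all loss before T1 is post-randomisation loss. The Abstract describes a different order, and the two sections must be reconciled. Confidence is high on the order of events and low on any magnitude. The 5-30% loss, the 90% versus 75% completion and the correlation of 0.2-0.3 are all assumptions, because the protocol states no rates.

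The main cost is to the feasibility estimates: on the assumptions in step 5, a 10% drop-out among women with a baseline would appear as 19-28% when counted from randomisation. Bias in the between-group comparison is a risk only, and small against the standard error in the example. For a feasibility study this should be fixed; it does not invalidate the design.

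**What to change.** 1. **Reconcile** the Abstract and the Procedure on when women are randomised, and the Inclusion and Exclusion Criteria on prior sling use, so that one agreed criterion is used.
2. **Allocate in Qualtrics on submission of T1**, from a concealed 1:1 list, and disclose the arm on the existing T1 end page (S.7/S.9). This fits the Abstract and delays no arm-specific step in the templates.
3. **Ask eligibility before allocation:** prior sling use and workshop attendance on the S.2 page, and infant illness or disability at the start of T1. Keep the workshop item in T1 as well, to catch attendance after sign-up.
4. **Report two rates:** consent-to-T1 loss as a recruitment outcome, and T1-to-T3 loss as trial drop-out.

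The cost is a change to the Qualtrics set-up and a short amendment. Women do not learn their group in pregnancy, and more must consent to reach 50-60 randomised: 56-67 at an assumed 10% loss before T1, or 63-75 at 20%.

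If antenatal randomisation is kept, state that the arm is concealed from the woman until T1 is submitted, and report pre-T1 losses and exclusions by arm, separately from later drop-out.
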